### Power and sample calculation

We adopted a conservative approach for the first phase of the study to ensure more close qualitative feedback. Accordingly we calculated a sample size of 30 based in the recommendations for internal pilot studies from Kieser&Friede [51]. For the third phase, a significance level of 0.05, power of 0.8 and a minimal detectable difference of 0.5 and an expected drop-out of 15% was set, which resulted according to the design in two arms of 74 patients each [52].

### Statistical analysis

During the first phase, a descriptive analysis of socio-demographic and clinical variables will be conducted, including mean age, sex, marital status, employment status, family psychiatric history, follow up time, number of episodes, predominant polarity, substance abuse and comorbid medical and psychiatric diagnoses. Feasibility will be evaluated analyzing the frequency of daily and weekly tests completed, if important differences in baseline characteristics between adherent and not adherent users are detected, this will be further controlled by regression analyses. The results of the satisfaction survey will be estimated analyzing the percentage of answers and the differences among the different categories using Chi-square analysis. Additionally, a Pearson correlation analysis will be carried out between the results of the assessments during the 3 month period and the results of the application tests to evaluate the clinical reliability between the two methods.

At the third phase, survival analysis with multivariate data analysis will be carried out to assess several covariates simultaneously and explore relationships between socio-demographic, clinical variables and assessments scores with relapses in each group (Kaplan-Meier). Similarly, differences among the different assessments will be analyzed with multivariate survival analysis (Cox regression). Similarly as in the first phase, a Pearson correlation analysis will be carried out between the results of the assessments and completed application tests. All the analyses will be two-tailed with an alpha set at p < 0.05. Additionally, last observation carried-forward intention to treat analyses will be performed.

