### Application development

During one year (May 2013 to May 2014) a collaborative team of specialists in bipolar disorder (psychiatrists and psychologists from the Bipolar Disorders Program of the Hospital Clínic of Barcelona) and software engineers as well as graphical designers held periodical meetings in order to determine the design of an online tool to monitor and register signs and symptoms of bipolar disorder and offer personalized psychoeducation contents. At the end of this process, the team resolved to develop a smartphone application with the following characteristics: user-friendly, non-stigmatizing and sensitive enough to detect mood changes in order to give customized psychoeducational feedback based on an existing psychoeducation group treatment manual [38], which has been previously tested by the Barcelona Bipolar Disorders Program [6].

Several evidence-based methods for self-mood assessment were considered taking into account the aims of the project. We chose 5 daily key questions balancing sensitivity and privacy, which are intended to be answered in a few seconds with the aid of an animated graphical interface (i.e. mood, energy, sleep time, irritability and medication adherence). If a relevant mood change is detected by means of an algorithm that takes into consideration the previous week mean score of the daily test, the user is requested to answer a more comprehensive second test based on the DSM-5 [39] criteria for mania, hypomania or depression, along with some extra questions regarding substance use and suicide risk. If the patient gives an affirmative answer to the question that explores suicidal ideation, an automatic e-mail message is sent to the mental healthcare team and in addition, an immediate call to emergency services is offered. Otherwise, if the subject is stable during their daily assessments, this DSM5 based test is requested to be answered only once a week.

Furthermore, the application will give feedback with a graphic showing daily mood changes and the user will be able to review the results of previous tests. Personalized daily psychoeducative messages will be sent based on the patient’s answers. The user will be able to customize the best time of the day to answer the test and to receive the psychoeducative messages at his or her convenience (Figure 2).

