**Figure 2 Fig2:**
[figure not shown]
**The chart shows the way in which the application SIMPLe 1.0 gives psychoeducative messages based on the answers of daily and weekly tests.**

Simultaneously, a web-based interface will be developed to allow the mental healthcare team to follow and monitor patient status.

The collaborative team decided that it was necessary a first study to determine the acceptability and validity of an application based solely on subjective information (SIMPLE 1.0), prior to the addition of objective monitoring data modules (SIMPLE 2.0) for three reasons: 1. In order to give patients active participation in the development of the application through focus groups and satisfaction surveys based on the experience with the first SIMPLE version and adapt the application to their preferences; 2. To test data safety and confidentiality issues with a smaller sample; 3. To adjust possible mood sensitivity issues with the daily and weekly questionnaires which were not previously validated in a real-world clinical setting (Figure 3).

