**Screenshots of SIMPLe 1.0 running in an Android Smartphone.**

### Study design and phases

The studies to evaluate the smartphone application will be carried out in three different but complementary phases as detailed below.**First phase:** A three months lasting feasibility study will be conducted in order to evaluate the use, reliability and patient satisfaction with symptom monitoring (subjective information). Patients under usual treatment will use a smartphone with the SIMPLe version 1.0 application installed. The intervention will be consecutively offered to 30 stable adults (>18 years) fulfilling the inclusion criteria described below. An informed consent will be handled and explained and must be signed in order to participate. Sociodemographic data and standardized clinical as well as functional assessments will be administered at baseline and monthly for three months. Assessments will include present manic symptoms using the Young Mania Rating Scale (YMRS) [40,41], depressive symptoms using the Hamilton depression Rating Scale (HDRS) [42,43], biological rhythms using the biological rhythms interview of assessment in neuropsychiatry (BRIAN) [44,45] and treatment adherence using the Morisky Green 8-item test [46]. A smartphone device with the SIMPLe 1.0 application pre-installed, will be given to the participants for free during the study with the mandatory condition that it has to be their main mobile-phone during the next 3 months. In the case the patient accepts to participate but doesn’t want to switch from his/her current smartphone, he/she will be offered the possibility to download the SIMPLe 1.0 application from the Application Store and a username and password will be given. The subject will receive a customizable automatic reminder in their smartphone to answer both daily and weekly questionnaires based on DSM-5 criteria for a manic, hypomanic, mixed or depressive episodes. The data obtained will be registered online. During this period of time, the subjects will receive daily customized psychoeducative messages based on the information collected by the application using an algorithm designed by our team. Feasibility and satisfaction will be assessed with the application usage log data and with an electronic survey. Reliability will be analyzed comparing the clinical assessments made by a psychiatrist and the information about mood state collected by the application**Second phase:** Three different focus groups (patients, psychiatrists and psychologists, software engineers and graphical designers) of 3 sessions each will be held to discuss the experience with the SIMPLE 1.0 app and recollect suggestions and bugs. Additionally, individual personal interviews with each SIMPLE 1.0 user will also collect qualitative information about the application and suggestions. Taking into consideration the information collected from participants in the first phase, the application will be adapted and improved with the addition of objective information (signs) monitoring modules using mobile usage parameters and the built-in actimetry sensors.**Third phase:** A six months randomized controlled trial with an intervention and a control arm including 74 patients each. An initial evaluation in both groups will be carried out recollecting sociodemographic data and using standardized clinical as well as functional assessments. This evaluation will be repeated at three, six and twelve months from baseline. The assessments will include present manic symptoms using the Young Mania Rating Scale (YMRS), depressive symptoms using the Hamilton depression Rating Scale (HDRS), functional impairment using the Functioning assessment short test (FAST) [47], biological rhythms using the biological rhythms interview of assessment in neuropsychiatry (BRIAN), quality of life measured by World Health Organization quality of life assessment (WHOQOL-BREF) [48] and treatment adherence using the Morisky Green 8-item test. During the follow-up the number of relapses, inpatient admissions, outpatient consultations, emergency rooms consultations and suicide attempts will be registered.**Intervention arm (SIMPLe 2.0 + TAU):** The experimental group will use the application SIMPLe 2.0 and will keep receiving their usual pharmacological treatment. A smartphone device with the SIMPLe 2.0 application pre-installed, will be given to the participants for free during the study with the mandatory condition that it has to be their main mobile-phone during the next 3 months. In the case the patient accepts to participate but does not want to switch from their current smartphone, they will be offered the possibility to download the SIMPLe 2.0 application from the Application Store and a username and password will be assigned. The self-mood assessments will adopt a similar approach to the SIMPLe 1.0 app. Additionally this information will be complemented with automatically recorded patients activity data which will include smartphone usage, telephone calls made (number of independent calls and total time), social network apps usage, and physical activity measured by the built-in actimeter. Patients will receive daily psychoeducative messages based on the data recollected by the application. Relapse risk will be calculated using an algorithm including both subjective and objective data. The clinical team will be contacted with an e-mail if there is moderate or high risk for an oncoming episode and the patient will be offered the outpatient or emergency for assistance.**Treatment as usual arm (TAU):** The treatment as usual (TAU) group will be followed-up with their standard treatment following the Barcelona Bipolar Disorders Program protocol [49].

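### Pearson correlation alone cannot show whether the app tracks or detects mood change within a patient, and its test is too liberal if repeated visits are pooled

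*Protocol article*

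**What the plan says.** In the Protocol article, the Statistical analysis section plans for the first phase that "a Pearson correlation analysis will be carried out between the results of the assessments during the 3 month period and the results of the application" (that is, its mood questionnaires), with the stated purpose "to evaluate the clinical reliability between the two methods". For the third phase it adds: "Similarly as in the first phase, a Pearson correlation analysis will be carried out between the results of the assessments and completed application tests". All tests are two-sided at the 5% level.

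Study design and phases gives the same aim in general terms: "Reliability will be analyzed comparing the clinical assessments made by a psychiatrist and the information about mood state collected by the application". It also fixes the data structure for the first phase: "The intervention will be consecutively offered to 30 stable adults", and "Sociodemographic data and standardized clinical as well as functional assessments will be administered at baseline and monthly for three months".

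No other method is named for this comparison. The article does not say how several visits from one patient enter the correlation.

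On what the app has to do, Application development wants it "sensitive enough to detect mood changes", using an algorithm that sets a user's daily answers against that user's own mean for the week before. The text after Figure 2 gives three reasons for running a first study. The third is "To adjust possible mood sensitivity issues with the daily and weekly questionnaires which were not previously validated in a real-world clinical setting".

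**The concern.** The app is built to notice change in one person over time. A plain Pearson correlation answers a different question: whether, across all the points supplied, higher clinician scores go with higher app scores in a straight line. Three consequences follow.

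- Stable differences between patients can produce a sizeable r even when the app follows nobody's mood over time.
- A constant under-reading by the app leaves r unchanged but lowers the share of episodes it picks up.
- Each patient supplies several visits. If these are pooled, the ordinary test counts them as independent and the p-value and interval are too optimistic.

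At stake is what the first phase can say about questionnaires that the article describes as not yet validated, and the same reading of the app data in the third phase.

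**Working it through.** The plan gives no figure for the correlation, so there is none to reproduce. The checks below use its design figures and stated assumptions.

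**Inputs from the article:** 30 patients; assessments at baseline and at months 1, 2 and 3; two-sided 5% level. Patients receive the app on entry, so baseline normally has no app data to pair with. That leaves m = 3 pairs per patient, or 30 × 3 = 90 pairs.

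**Assumed, because the article does not give it:** the intraclass correlation (ICC) of clinician score and app score, equal in both, from 0 to 0.9.

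**Step 1: between and within patients.** For pooled pairs,

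r = √(ICCx·ICCy)·ρ_between + √((1−ICCx)(1−ICCy))·ρ_within.

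Set ρ_within = 0, so the app follows no one over time, and let ρ_between be as high as 1. Then r can reach √(ICCx·ICCy), which is 0.3, 0.5, 0.7 or 0.9 at those ICCs. A large r is possible with no within-patient tracking.

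**Step 2: shift in the app score.** Take bivariate normal scores with r = 0.8 and an episode defined, for illustration, as more than 1 SD above the mean on either measure (simulated):

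| App level | r | Sensitivity | Specificity |
|---|---|---|---|
| same as clinician | 0.8 | 0.62 | 0.93 |
| 0.5 SD low | 0.8 | 0.34 | 0.98 |
| 1 SD low | 0.8 | 0.13 | 1.00 |

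The correlation is identical in all three rows, while sensitivity falls from 0.62 to 0.13.

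**Step 3: the test, if visits are pooled.** With no true association, the variance of r is inflated by about

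V = 1 + (m − 1)·ICCx·ICCy,

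and the real error rate of the nominal 5% test is about 2·P(Z > 1.96/√V). For m = 3:

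| ICC (both) | V | Error, formula | Error, simulation (30 × 3, 10,000 runs) | Equivalent independent pairs (90/V) |
|---|---|---|---|---|
| 0 | 1.00 | 0.050 | 0.047 | 90 |
| 0.3 | 1 + 2·0.09 = 1.18 | 0.071 | 0.070 | 76 |
| 0.5 | 1 + 2·0.25 = 1.50 | 0.110 | 0.109 | 60 |
| 0.7 | 1 + 2·0.49 = 1.98 | 0.164 | 0.165 | 45 |
| 0.9 | 1 + 2·0.81 = 2.62 | 0.226 | 0.237 | 34 |

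If either ICC is zero, the product vanishes, V = 1 and the error stays at 5%. With one pair per patient (n = 30), the simulated error was 0.047 to 0.051 at every ICC.

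For the third phase, assume that all 74 intervention patients have app data at three post-baseline visits. Simulation then gives 0.071, 0.112, 0.164 and 0.228 at ICC 0.3, 0.5, 0.7 and 0.9. More patients do not cure the problem.

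**The case against.** The strongest reply is that pooling is inferred. One correlation per visit, or one mean per patient, fits the same sentence and gives no inflation. The unit of analysis is also something a condensed article may leave to a fuller document. This stands, so the error-rate part is conditional. A reader might infer that the planned p-values are certainly too small, but the text does not establish that. The reply does not rescue the method itself, which the article does fix. Means per patient discard within-patient change altogether, and a single-visit correlation cannot separate it from stable differences between patients.

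The size is also open. The ICC is assumed. If selecting stable patients mainly narrows the spread between them, the ICC falls and the inflation with it. Figures for four pairs per patient would be higher, but they fit poorly because baseline precedes app use. In any case a test of r = 0 is secondary for reliability: the size of r matters more, and clustering by itself does not bias the pooled r as an estimate of the total correlation.

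A reader might further infer that this correlation decides how the app raises alerts in the randomised trial. The article does not say so. Sensitivity adjustment is the third of three reasons for the first study, and no section makes r a decision rule. The app is revised through focus groups, interviews and participants' information. The third-phase risk algorithm also uses objective data that the first version does not collect.

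Finally, with 30 stable patients followed for three months, few episodes are likely, so an estimate of sensitivity will be imprecise. That is true. It is a reason to show the interval, not a reason to rely on r.

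**Conclusion.** The point holds in a limited form. Without any assumption about pooling or ICC, Pearson's r alone does not isolate within-patient tracking, does not react to a shift or rescaling of the app score, and gives no missed-episode or false-alarm rate. It therefore cannot by itself support the sensitivity adjustment named as one purpose of the first study.

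Conditionally, if post-baseline visits are pooled as independent pairs, the nominal 5% test has a real error of about 7% to 24% for an ICC of 0.3 to 0.9 in both measures (11% to 16% at 0.5 to 0.7), and 5% if either ICC is zero.

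This concerns a validation analysis in both phases. It should be changed, but it is no threat to the main result: the randomised comparison of relapses does not use this correlation.

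**What to change.** In both phases, replace the plain Pearson test with a repeated-measures correlation, or a mixed model with patient as the cluster, that reports within-patient and between-patient association separately. Take intervals from a bootstrap that resamples patients. State which app tests are paired with which visit.

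As a descriptive addition, cross-tabulate the app's mood-change flag, or the result of its DSM-5-based test, against the clinician's rating at the matching visit. Report sensitivity and specificity with patient-clustered intervals. Two things must be settled first:

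- **Stability cut-offs.** Sample recruitment gives YMRS ≤ 8 and HDRS ≤ 6, whereas Inclusion criteria gives HDRS ≤ 8 and YMRS ≤ 6. These must be reconciled before either can serve as a reference.
- **Reference and time window.** The app's flag marks change from the previous week, while a cut-off marks level on the day of the visit. The plan should say which app output is compared with which clinician standard, and over what window.

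The cost is revised analysis wording plus these definitions; no new assessments are needed. At the time of the article the first phase had not yet started with patients. The downside is wider intervals: under the null, by a factor of about √1.50 = 1.22 to √1.98 = 1.41 at ICC 0.5 to 0.7 compared with pooling. The sensitivity estimate from 30 stable patients will also be imprecise.

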
### Participants

#### Sample recruitment

The participation in the study will be offered to stable bipolar patients (YMRS ≤ 8, HDRS ≤ 6 for at least one month prior to study entry) who had experienced at least one hypomanic, manic or depressive relapse during the 12 months prior to the study entry. All the participants will be adult patients attending the outpatient mental health clinic of the Hospital Clinic of Barcelona. All participants in both groups must read and agree with the terms and sign an informed consent prior to their inclusion in the study.

The following selection criteria will be considered for the first and third phase:

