#### Inclusion criteria

1. Age from 18 to 65 years old, 2. Patients with a current diagnosis of Bipolar disorder type I or type II according to DSM-5 criteria and confirmed with a semi-structured interview (SCID), 3. Hamilton Depression Scale score under or equal to 8 during the last month, 4. Young Mania Rating Scale score under or equal to 6 during the last month, 5. No history of relapses during the previous 3 months but at least 1 relapse during the last year, and 6. Availability of an unlimited smartphone data plan during the 12 following months to avoid extra costs for the participants when using the application.

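### LOCF is the only named intention-to-treat method, in patients who all enter stable; for symptom and functioning scores this understates worsening and distorts the comparison if drop-out differs by arm

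*Protocol article*

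**What the plan says.** The Statistical analysis section analyses third-phase relapses by survival methods (Kaplan-Meier, with Cox regression also named), sets the test level ("All the analyses will be two-tailed with an alpha set at p < 0.05"), and then adds: "Additionally, last observation carried-forward intention to treat analyses will be performed". It does not say which outcomes that sentence covers.

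The design around it is as follows.

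- **Entry state.** Sample recruitment offers the study to "stable bipolar patients (YMRS ≤ 8, HDRS ≤ 6 for at least one month prior to study entry". The Inclusion criteria add: "No history of relapses during the previous 3 months but at least 1 relapse during the last year". The Exclusion criteria remove patients with a FAST score of 20 or more.
- **Assessments.** After the initial evaluation, Study design and phases says: "This evaluation will be repeated at three, six and twelve months from baseline". Relapses, admissions and suicide attempts are registered during follow-up.
- **Drop-out.** Power and sample calculation says that "a significance level of 0.05, power of 0.8 and a minimal detectable difference of 0.5 and an expected drop-out of 15% was set", giving "two arms of 74 patients each".

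**The concern.** LOCF assumes that a patient's score stays where it was last seen. In a relapse-prevention trial of stable patients, the last score before loss is usually a good one, while the disorder is episodic and the trial exists because some patients will worsen. Carrying that score to the end records drop-outs as well over time in which nobody observed them. It also enters imputed scores as if they had been measured.

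The between-arm result is at stake when loss is unequal, because the arm with more carried-forward remitted scores gains. Unequal loss is plausible here. Only the application arm has daily tests, automatic activity recording and, for those who accept it, a supplied phone that must be their main one. Only application users can be considered for exclusion after a risk situation is detected through the application (Randomization, data anonymization and blinding). A patient removed as an episode begins would be carried forward at an earlier, better score.

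**Working it through.** **1. The plan's own figure.** Inputs from Power and sample calculation: two-sided alpha 0.05, power 0.80, difference 0.5 (scale not stated; read as standardised, SD 1), drop-out 15%.

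- n per arm = 2 × ((1.960 + 0.842)/0.5)² = 62.79
- 62.79/0.85 = 73.87, rounded up to 74, as stated
- Expected losses: 74 × 0.15 = 11.1 per arm. Expected completers: 74 × 0.85 = 62.9 per arm, with power 80.1%.

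An LOCF analysis would present 74 final scores per arm when about 63 were observed.

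**2. What drop-outs would carry forward.** The article gives no relapse rate, so this is a simulation under assumptions: exponential relapse and drop-out over 12 months, 15% drop-out, last attended visit at 0, 3 or 6 months.

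| Assumed 12-month relapse | Drop-outs with a relapse before their last attended visit | Same, if drop-out risk doubles after relapse |
|---|---|---|
| 30% | 10.1% | 16.4% |
| 40% | 13.9% | 21.6% |
| 50% | 18.1% | 27.1% |
| 60% | 22.8% | 32.7% |

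So roughly 77 to 90% of drop-outs (67 to 84% with the doubled risk) have no relapse by the visit carried forward. About a quarter (22 to 27%) have only the baseline value.

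**3. Effect on a score, with no true effect.** Assumptions: 40% relapse in both arms, endpoint HDRS 18 for relapsers and 4 for others, drop-outs at the same risk as completers, every drop-out carrying 4. Full-data mean = 0.4 × 18 + 0.6 × 4 = 9.6. LOCF mean = (1 − d) × 9.6 + d × 4.

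| Loss, app / TAU | LOCF mean, app | LOCF mean, TAU | False difference |
|---|---|---|---|
| 15% / 15% | 8.76 | 8.76 | 0 |
| 20% / 10% | 8.48 | 9.04 | 0.56 in favour of app |
| 25% / 5% | 8.20 | 9.32 | 1.12 in favour of app |
| 10% / 20% | 9.04 | 8.48 | 0.56 against app |

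Two milder assumptions give less at a 10-point gap in loss:

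- If 13.9% of drop-outs carry 18 (step 2, 40% row), the carried mean is 4 + 14 × 0.139 = 5.95, and the false difference is 0.10 × (9.6 − 5.95) = 0.37.
- If scores instead worsen linearly by 2 to 6 points over 12 months and losses are uniform in time, drop-outs carry on average 0.25 × 0 + 0.25 × 0.25 + 0.5 × 0.5 = 0.3125 of the change. The false difference is 0.10 × 0.6875 × 2 = 0.14 to 0.10 × 0.6875 × 6 = 0.41.

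**4. Equal loss with a true effect.** With relapse of 40% and 20%, the full-data means are 9.6 and 4 + 14 × 0.2 = 6.8, a difference of 2.8. With 15% loss in both arms and every drop-out carrying 4, it becomes 0.85 × 2.8 = 2.38.

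**5. Relapse, only if LOCF were applied to relapse status.** If every drop-out counted as relapse-free, the apparent risk is (1 − d) × 0.40. Losses of 20% and 10% show 32% and 36%; losses of 25% and 5% show 30% and 38%. If 13.9% of drop-outs have a recorded relapse, the false gaps fall from 4 and 8 points to 0.10 × (0.40 − 0.139) = 2.6 and 0.20 × 0.261 = 5.2 points.

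**The case against.** The best defence is that the sentence comes last, as an addition to survival analyses that already handle loss by censoring, and that a condensed article leaves missing-data detail to a fuller document. Part of this stands: the article does not say that LOCF is the main analysis, and nothing says that the survival analysis leaves out randomised patients. The appeal to condensation does not rescue the sentence, because the article does not leave the method open. It names LOCF, and names no other intention-to-treat method.

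A reader might infer more than the text supports, in three ways.

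- **That every drop-out is recorded as well.** LOCF carries whatever was last seen. With visits at 3 and 6 months, and relapses registered throughout, later drop-outs can carry a symptomatic score or a recorded relapse.
- **That the relapse result is biased.** Kaplan-Meier and Cox ordinarily censor drop-outs. The percentages in step 5 belong to an analysis that the article does not describe, though its wording does not rule it out.
- **That the bias favours the application.** Drop-out is not given by arm. A supplied phone and daily contact could equally improve retention, and the bias would then run against the application. The TAU arm is not left without care; it follows the programme's standard treatment.

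The HDRS illustration is also near a ceiling, since it needs every relapse to be depressive and still present at the endpoint.

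**Conclusion.** The point holds for symptom and functioning scores. LOCF is a poorly chosen stated method here: it records most drop-outs as remitted, understates worsening in each arm, and overstates how much was observed. It also shrinks a true difference under equal loss (2.8 to 2.38 in the example).

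A false between-arm difference is conditional. It needs unequal loss, and it favours whichever arm loses more patients. Its size at 20% and 10% loss is about 0.6 HDRS points near the upper end, and 0.14 to 0.41 under milder assumptions. It is zero when loss is equal and there is no true effect. The relapse rates, endpoint scores and split of losses are all assumed; only the overall 15% is the plan's.

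For relapse the finding is an ambiguity: the article should say that LOCF does not apply to relapse status.

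The YMRS and HDRS entry limits are interchanged between Sample recruitment and the Inclusion criteria and must be reconciled. Patients are stable under either version, so this point is unaffected.

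**What to change.** Replace the LOCF sentence with three statements.

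1. Time to relapse is analysed in all randomised patients, by arm as randomised. Drop-outs are censored at last contact and not carried forward as relapse-free, and the assumption that censoring is uninformative is examined.
2. Scores are analysed with a likelihood-based mixed model for repeated measures on all observed 3-, 6- and 12-month data, with arm, visit, arm-by-visit interaction and baseline score. This relies on data being missing at random.
3. Because that assumption may fail when patients leave during an episode, a sensitivity analysis lets drop-outs do worse, for example by delta-adjusted multiple imputation.

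The cost is wording and modest extra programming. No new data are needed, and 74 per arm stands because it already allows for 15% drop-out. The Trial status section reports that even the first phase had not begun with patients, so the change can be made before any third-phase data exist.
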